#### Phase I–Retrospective data collection, facility surveys, and FGDs in the community

Two-year retrospective data (01 January 2020 to 31 December 2021) will be collected from all the public health facilities in study areas where snakebite management is expected to be provided. This includes all the Primary Health Centers, Rural Hospitals / Community Health Centers, Sub District Hospitals and District Hospitals. Medical Colleges where severe cases are referred from the study blocks will also be included to ensure quality retrospective data collection. Additional data on snakebite deaths will also be collected from local authorities, panchayat office, registrar of births and deaths so that maximum deaths are captured. A cross-sectional survey will assess the preparedness of the public health facilities for SBE management. Retrospective data and facility data will be collected and entered into an online application. The captured data will be verified at regular intervals by the study coordinator.

The qualitative component will involve conducting community FGDs in the study areas. Total 24 FGDs will be conducted, six per block (three male, three female). Each FGD will be restricted to 8 to 16 participants. Actual number of FGDs may vary according to the saturation of responses. FGDs will be conducted at common and acceptable community places. The Primary Health Centers (PHCs) in the block would be enlisted and one random village would be picked per PHC. The information about conduct of a FGD would be given to the villagers with the help of the frontline community healthcare workers and community leaders and 8–16 randomly selected participants would be invited to participate. Participants belonging to the community and above 18 years of age will be included for FGDs. Healthcare providers will be excluded.

#### Phase II—Development and implementation of an educational intervention

Educational interventions in the form of printed IEC material will be developed based on the gaps identified during the FGDs and a review of the literature. The TAC will review the IEC material based on the relevance and ease of understanding for the target population. Commonly occurring words in the local language along with pictorial/cartoon messages will be used in the IEC material. Contact numbers of public health facilities will be included. Short information videos about immediate first aid and early referral will be developed and circulated among the community members. Videos regarding immediate care of a snakebite victim at the facility will be circulated among the healthcare providers. Pilot intervention procedures will be implemented to know the community’s understanding and accordingly further intervention procedures will be carried out by trained staff. The final revised version of the IEC will be assessed for ease of readability using the SMOG index. All educational tools will be validated with the help of the Technical Advisory Committee, herpetologists and subject experts.

IEC materials will be distributed at key places like village panchayats, forest departments, local faith healers, school teachers, community leaders, anganwadis, tribal residential schools, Sub-Centers (SCs), PHCs, and other health facilities. With the help of local health officials and ASHAs, community meetings and talks would be held at each study site during *gram sabha* (village gatherings), community program and religious events. Informative posters would also be put up at places where people gather routinely like tea stalls or local restaurants. Prevention measures to be employed for snakebite prevention in the communities will be as per the Standard Treatment Guidelines, (STG,2017).

#### Phase III—Evaluation of the healthcare providers

Assessment of the basic knowledge, awareness, and perceptions on snakebite management and preventions among healthcare providers will be conducted. All the Medical Officers and Peripheral Health Workers from the study blocks who agree to participate will be included in the study. Each block will have approximately 40 MOs; so nearly 160 MOs will be assessed during the study. Similarly, around 600 peripheral workers (150 per block) will also be evaluated. Actual numbers may vary as the MOs or healthcare workers are frequently transferred in the health system.

#### Phase IV—Capacity building of healthcare providers

The capacity building of healthcare providers will be done by periodic short term training programs. A team of national experts for snakebite management (Expert group STG, 2017) will provide training to master trainers at each study site. Total six master trainers, including two from State Public Health Department, two Senior MOs from SDH/DH, and two MOs from PHC/RH/CHC, will be trained per block. The training will involve lectures and practical demonstrations to cover all aspects of snakebite management including signs and symptoms of SBE, how to suspect/recognize snakebite, management of sever cases, anti-venom use, laboratory examinations, referral and discharge criteria. Knowledge gaps identified in phase III will also be covered in the training sessions.

All master trainers will be provided quick reference guides and treatment flyers, prepared as per the STG, 2017. The master trainers along with site investigators will conduct training programs for all the MOs every six months for two years. The national expert team will provide technical support for these regional trainings. Trained MOs will further train around 600 ASHAs, Auxiliary Nurse Midwives (ANMs) and Multipurpose Workers (MPWs) at their respective health facilities on first aid skills, immobilization techniques and cardiopulmonary resuscitation. Quick reference charts as per STG (2017) and training manuals in regional languages will be given to healthcare providers and also displayed in examination rooms and indoor wards of health facilities. Site investigators will make periodic visits to health facilities for supportive supervision, post-training follow up and grievance redressal.

#### Phase V—Impact evaluation of interventions

FGDs will be conducted in the study areas to evaluate the post-intervention community knowledge with the same methodology as discussed in Phase I, two months after the educational intervention. Pre- and post-training evaluations will be done to assess knowledge retention and the impact of training on the healthcare providers. Prospective data will be collected from the health facilities after the capacity building training of Medical Officers in study blocks for a period of one year. Incidence and case fatality rate in the study blocks will be calculated based on the prospective data. The impact of capacity building on the healthcare system will be assessed by comparing prospective data with the retrospective (pre-intervention) data.

### Ethics and dissemination

Ethics approval was obtained from the Institutional Ethics committee of ICMR- NIRRCH (Ref. No. D/ICEC/Sci-194/209/2021) and ICMR-RMRCB (ICMR-RMRCB/IHEC-2021/79). The study is registered under the Clinical Trial Registry India no. CTRI/2021/11/038137. Ethics committees of ICMR-NIRRCH and ICMR-RMRCB will supervise data monitoring and trial conduct. Written informed consent will be taken from each participant in the vernacular language before inclusion. Permissions are obtained from the Public Health Authorities for the implementation of the study. Approval of all investigators and Ethics Committees will be sought before any major modifications or amendments to the protocol are implemented. Minor changes will be approved by the investigators and the same would be notified to the Ethics Committees before implementation. The results from this study will be disseminated with local, state, and national health authorities, and the general population on the study website, social media as well as through scientific meetings, media reports and publications.

### Confidentiality and data storage

A central database to capture all the generated data will be developed and maintained at ICMR-NIRRCH, Mumbai. Qualitative data including audio recordings and transcripts will be kept separately and all the records that identify the participants will be kept confidential. Data will be secured as per the ICMR National Guidelines for Biomedical and Health Research Involving Human Participants [31]. Data entry and data verification will be carried out independently. Data will be backed up regularly in hard drives with sufficient memory space. RG will have ultimate authority over the study dataset.

### Statistical analysis

The baseline data will be analyzed separately for different strata (Gender-wise, Age-wise, seasonal variation, distribution of venomous and non-venomous snakebite, site of snakebites, and categorization of snakebite based on the sign and symptoms of envenomation). The differences across strata will be investigated using appropriate statistical tests based on the nature of the variables. The Chi square and Fisher’s Test would be used to compare categorical variables while the independent t-test would be used to compare continuous variables. To check the factors associated with the incidence of snakebite, bivariate regression models will be used and results will be presented through odds ratios. The primary outcome will be reduction in the incidence of snakebite cases per 100000 population and a reduction in the case fatality rate in the study areas at the end of two years, measured by comparing the pre- and post-intervention data on the incidence of snakebite and mortality in the four study blocks. The secondary outcomes will include reduction in mean bite to needle time, reduction in the proportion of snakebite victims referred to higher facilities for management, increase in the proportion of MOs providing treatment as per STG 2017, mean increase in the number of vials of anti-venom administered to victims, reduction in the proportion of cases with severe complications including reduced kidney failure and amputation rate. Data from interviews of healthcare providers will be analyzed further for frequency. A summative index will be developed from the knowledge test of health workers. Two sample t-test will be used to compare the change in the knowledge of Medical Officers and the healthcare workers after the training. A p-value < 0.05 will be considered statistically significant. All the quantitative data will be entered and analyzed using the statistical package SPSS (version 26.0; IBM Corporation, Armonk, NY, USA).

Change in knowledge and awareness of the community will be assessed through pre-and post-intervention FGDs. Audios of the participants’ discussion will be recorded and notes will be taken. Transcripts will be proofread and then translated to English by the project staff. The transcriptions and translations will be cross checked by a senior project staff to ensure accuracy. A sample of the corrected translations will be read by the investigators to identify themes and subthemes using an inductive approach. Any additional themes or sub-themes after descriptive content analysis will also be identified. Disparities in the sub-themes or themes will be discussed by the investigators and consensus will be sought on the definitions of codes. Coding for the transcripts, based on the consensus definitions, will be carried out by two experienced staff members. All the coded transcripts will be reviewed for quality, consistency and accuracy. Broad themes based on similar ideas will be merged. Findings by major themes will be summarized. Important respondent narratives will be marked for future citations. A directory of the snakes found in the study blocks along with their local names will be created. Qualitative data analysis will be carried out using *NVivo* software (QSR International, UK).

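### The two-sample t-test fixed for knowledge change ignores repeat testing of the same providers and facility grouping; before/after patient outcomes share the grouping problem if the other named tests are carried over

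*Protocol article*

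**What the plan says.** All the relevant wording on tests is in the protocol article under Statistical analysis.

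- **Knowledge.** A summative index is built from the knowledge test, and "Two sample t-test will be used to compare the change in the knowledge of Medical Officers and the healthcare workers after the training". This is the only test tied explicitly to a before/after comparison.
- **General tests.** Chi-square and Fisher's "Test would be used to compare categorical variables while the independent t-test would be used to compare continuous variables". This directly follows the baseline text: "The differences across strata will be investigated using appropriate statistical tests based on the nature of the variables".
- **Primary outcomes.** Incidence and case fatality are "measured by comparing the pre- and post-intervention data on the incidence of snakebite and mortality in the four study blocks". No test is attached.
- **Secondary outcomes.** "The secondary outcomes will include reduction in mean bite to needle time, reduction in the proportion of snakebite victims referred to higher facilities for management", followed by treatment according to the guideline, vials of anti-venom and severe complications. No test is attached here either.
- **Significance.** "A p-value < 0.05 will be considered statistically significant".

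The data structure is described elsewhere. Phase V evaluates providers before and after training. In Phase IV, "Trained MOs will further train around 600 ASHAs" and other peripheral staff at their own health facilities, while Medical Officers (MOs) are trained by master trainers (six per block) and site investigators. In Phase I, patient data "will be collected from all the public health facilities in study areas where snakebite management is expected to be provided"; in Phase V they come from health facilities in the same blocks. Phase III expects about 160 MOs and 600 peripheral workers and warns that staff are often transferred. Clustering, facility or block effects and pairing are not mentioned.

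**The concern.** A two-sample t-test assumes that the pre-training and post-training scores come from two independent sets of independent people. Neither part of that holds here. Largely the same staff are tested twice, so their scores are correlated. Peripheral workers trained together by the same MOs are likely to improve, or fail to improve, together. Ignoring the first makes the standard error too large; ignoring the second makes it too small. The reported p-value therefore does not have its stated meaning, and the direction of the error depends on which effect dominates.

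The patient outcomes carry a related risk. Referral, bite-to-needle time and adherence to the guideline are facility practices. If training takes hold unevenly, each facility's change has its own random component, which a test on pooled individuals leaves out. The blocks also differ widely: Table 1 gives populations from 70,542 to 314,103 and rural shares from 67% to 100%. If blocks are pooled without adjustment, a shift in block mix between periods can look like a change over time. The results are intended to support upscaling to other states, so a falsely significant improvement would have consequences.

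**Working it through.** The document states no sample size, intraclass correlation or number of facilities, so there is no figure of its own to reproduce. The check asks what the actual type I error is when a test for independent observations is applied to before/after data from the same facilities.

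**Inputs from the document:** significance level 0.05 (taken as two-sided); about 160 MOs; about 600 peripheral workers.

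**Assumed inputs:** 40 facilities, giving 160/40 = 4 MOs and 600/40 = 15 peripheral workers per facility; m people per facility and period; within-period intraclass correlation r; cluster autocorrelation c (1 means that facility effects are fully stable over time); correlation q between one worker's two scores.

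**Formulas.** VR is the true variance of the before/after difference divided by the variance that the test assumes.

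- Same people tested twice: VR = 1 + (m − 1)·r·(1 − c) − q
- Different people in each period: VR = 1 + (m − 1)·r − m·r·c
- Actual type I error = 2·[1 − Φ(1.96/√VR)]

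**Knowledge, same staff re-tested**

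| Group | m | r | c | q | VR | Type I error |
|---|---|---|---|---|---|---|
| MOs | 4 | 0.05 | 0.8 | 0.5 | 1 + 3·0.05·0.2 − 0.5 = 0.53 | 0.007 |
| Peripheral workers | 15 | 0.05 | 0.8 | 0.5 | 1 + 14·0.05·0.2 − 0.5 = 0.64 | 0.014 |
| Peripheral workers, weak pairing and uneven facilities | 15 | 0.10 | 0.5 | 0.3 | 1 + 14·0.10·0.5 − 0.3 = 1.40 | 0.098 |

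Simulated t-tests with 40 facilities gave 0.006, 0.014 and 0.100 for the three rows. If turnover were complete, so that different workers were tested each time, m = 15 and r = 0.05 would give 0.089, 0.062 and 0.044 at c = 0.5, 0.8 and 1.

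**Patient outcomes, different patients in each period, m = 20**

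| r | c = 0 | c = 0.5 | c = 0.8 | c = 1 |
|---|---|---|---|---|
| 0.05 | 0.161 | 0.104 | 0.068 | 0.044 |
| 0.10 | 0.250 | 0.155 | 0.086 | 0.039 |

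For example, at r = 0.05 and c = 0.5, VR = 1 + 19·0.05 − 20·0.05·0.5 = 1.45, which gives 0.104. The test is too liberal only when c is below (m − 1)/m, which is 0.95 at m = 20. Over m = 10 to 50 and r = 0.01 to 0.10, the full range is 0.039 to 0.42. Simulated t-tests at r = 0.05 gave 0.105, 0.059 and 0.039 at c = 0.5, 0.8 and 1.

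**Second route for a proportion.** A simulated pooled chi-square comparison assumed 1300 baseline and 650 follow-up patients, 35% referred and 40 facilities of unequal size. Type I error was about 5% when facilities did not differ in their change over time. It was about 8%, 14% and 26% when the SD of each facility's change was 0.3, 0.5 and 0.8 on the log-odds scale. With 20 facilities it was about 12%, 23% and 38%.

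**The case against.** The strongest reply is that the chi-square, Fisher and independent t-test sentence belongs to the baseline comparison across strata. No test is attached to the patient outcomes, and a condensed article may leave that choice to a fuller plan. This stands: the patient part of the point is conditional on those tests being carried over. It does not remove the knowledge part, because that test is named.

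A reader might infer that ignoring facilities makes all the before/after p-values too small. The documents do not support that. The same facilities are observed in both periods, so stable facility effects largely cancel. For re-tested staff, the neglected pairing usually makes p-values too large.

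A reader might also infer that the whole intervention is delivered by facility. In fact MOs are trained through master trainers organised by block, and community education runs through villages, schools and gatherings. Facility grouping by training applies firmly only to peripheral workers.

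The text does not say that blocks will be merged without adjustment, so the concern about block mix is a risk, not a stated error.

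Finally, the knowledge sentence could be read as contrasting the change in MOs with the change in other workers. That would take care of pairing, but it would not test whether training raised knowledge. The two groups also have separate questionnaires, which makes such a contrast hard to interpret.

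**Conclusion.** The point holds in two parts of unequal strength.

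First, the two-sample t-test for knowledge is a poor choice as fixed, because it ignores both the pairing within provider and, for peripheral workers, the facility grouping. Its error can go either way: about 0.7% to 1.4% actual type I error with moderate pairing and mild facility effects, which costs power, and about 10% with weak pairing and strongly uneven change.

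Second, if the other named tests are used for the before/after patient outcomes, they omit facility-by-period variation and possible shifts in block mix. Type I error is then about 4% to 5% with stable facilities and roughly 7% to 25% under moderate assumptions (m = 20, r = 0.05 to 0.10, c from 0.8 down to 0). It is higher with larger or fewer facilities.

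Every correlation, the number of facilities and the patient counts are assumptions. The document does not allow the size to be fixed, so the figures show direction and plausible range only.

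**What to change.** - **Knowledge.** Replace the two-sample t-test with an analysis of each provider's own change, or with a mixed model containing a worker effect, which also uses staff transferred in or out who have only one score. Include block as a fixed effect, and treat facility as the cluster for peripheral workers.
- **Before/after patient outcomes.** Use a regression suited to each outcome, with period and block as fixed effects and with standard errors or random effects that allow for facility and facility-by-period variation.
- **Chi-square, Fisher and independent t-tests.** State that they are for baseline description only.

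The cost is a few lines of analysis text. Facility identifiers must be kept for patients and staff, and each worker's two scores must be linked. Some confidence intervals will become wider; those for knowledge will often become narrower once pairing is used.

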**Fig 3 pone.0281809.g003:**
[figure not shown]
Geographical location of study areas of Maharashtra and Odisha states in India. Source: AMCHARTS SVG Maps; https://www.amcharts.com/svg-maps/?map=india2019. Permission obtained for use.

**Table 1 pone.0281809.t001:** Demographic details of the study areas in Maharashtra and Odisha.

Parameter	Shahapur block	Aheri block	Khordha block	Kasipur block
Coordinates	19.45°N 73.33°E	19.41°N 80.00°E	20.16°N 85.66°E	19.22°N 83.08°E
Population	314103	116992	139978	70542
Living in rural areas	77.5%	87.5%	67%	100%
Scheduled Tribes population	35.7%	49.8%	8.4%	58.8%
Female literacy	58.41%	55.67%	73.22%	20.35%
Sex ratio	957	986	935	1071
Workers engaged in marginal activities*	27.6%	29.8%	25.5%	60%

All data sourced from—Census of India 2011. Registrar General and Census Commissioner of India. https://www.censusindia.co.in/. Accessed 24 April 2022.

*Marginal activities provide livelihood for less than six months in a year. Proportions out of total working population in the block

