#### Development of data collection tools and their validation

The data collection tools will be developed by public health experts based on a review of available literature, standard treatment guidelines for snakebite, and consultation with the TAC.

*Retrospective and Prospective data form*. These two data collection forms will include questions about the basic demographic characteristics of the snakebite victim followed by details of the event of snakebite, signs and symptoms, first aid, and steps taken for the management including usage of anti-venom. The forms will have a separate ‘Follow Up’ section for transferred out patients. Hospital records will be used for form filling.

*Facility Survey Questionnaires*. Separate questionnaires will be developed for Primary Health Centre (PHC), Rural Hospital (RH) / Community Health Centers (CHC), and Sub District Hospital (SDH) / District Hospital (DH) to document staff positions, drugs, equipment, anti-venom availability and utilization, infrastructure, laboratory investigations, and Information Education Communication (IEC) materials and activities. The questionnaires will concur with the Indian Public Health Standards (IPHS) Guidelines and STG, 2017 for respective facilities.

*Focused Group Discussion (FGD) Guide*. The FGD guide will consist of open-ended, semi-structured questions to elicit the knowledge, awareness, and perceptions of people in the study area regarding snakes and snakebites, first aid, prevention methods, management, and health-seeking behavior. The FGD guide will be developed in English and later translated to local languages.

*Questionnaire for healthcare providers*. Separate questionnaires for peripheral workers and Medical Officers (MO) at facilities would be developed based on the STG, 2017 and WHO SEARO Guidelines for management of snakebites. They will try to capture the knowledge, perceptions, and experiences of healthcare providers regarding snakes and snake bites, anti-venom use, challenges encountered while managing snakebite cases at public health facilities.

All the developed tools will be validated through the following methods–

*Face Validity*. The TAC will critically review the tools to confirm that they have sufficient and pertinent information to gather the knowledge, awareness, and perceptions of the respondents. The panel will be asked to comment on the relevance, language, ease of understanding, and ability of the questions to elicit desired responses.

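### The odds ratios planned for snakebite incidence have no unbitten comparison: the individual records cover victims only, and the model is not tied to a population denominator

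*Protocol article*

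**What the plan says.** The analysis is fixed in the Statistical analysis section of the protocol article: "To check the factors associated with the incidence of snakebite, bivariate regression models will be used and results will be presented through odds ratios". The outcome is therefore the occurrence of a bite, the model is an unadjusted regression, and the effect measure is an odds ratio.

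The data are described elsewhere in the article:

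- **Retrospective and prospective forms** (Development of data collection tools and their validation): "These two data collection forms will include questions about the basic demographic characteristics of the snakebite victim followed by details of the event of snakebite". Their source is also given: "Hospital records will be used for form filling".
- **Baseline period** (Phase I; the quote stops before the sentence ends): "Two-year retrospective data (01 January 2020 to 31 December 2021) will be collected from all the public health facilities in study areas where snakebite management".
- **Supplementary source** (Phase I): "Additional data on snakebite deaths will also be collected from local authorities, panchayat office, registrar of births and deaths".
- **Post-intervention period** (Phase V; twelve months, the quote stopping one word short): "Prospective data will be collected from the health facilities after the capacity building training of Medical Officers in study blocks for a period of one".

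The primary outcome, in the Statistical analysis section, is a bite rate per 100,000 residents together with the case fatality rate. Table 1 gives block populations from the 2011 census.

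**The concern.** The outcome of this regression is whether a person was bitten. To estimate its odds ratio, the data must contain unbitten people, or the model must take the number of unbitten people from a population count. The article's individual records offer neither. Each form describes a victim, and the added death records are of snakebite deaths, so these people were bitten too.

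The other participants do not fill the gap. Focus group members contribute discussion that is coded by theme. Medical Officers and peripheral workers complete knowledge assessments. Neither group is described as a comparison group for bite risk.

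At stake is whether a named analysis can be run. If an odds ratio were nevertheless formed inside the victim data, it would describe who is found among recorded victims, or which victims had some further outcome. It would not describe who is at risk of being bitten.

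**Working it through.** The article gives no sample size, power or odds ratio for this analysis, so there is no stated figure to reproduce. The check is whether the odds ratio can be identified from the data described.

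**Step 1. The two-by-two table.** Let *a* and *c* be bitten people with and without a factor, and *b* and *d* unbitten people with and without it. The odds ratio is *ad/(bc)*. In victim-only records *b* = *d* = 0, so it is (*a* × 0)/(0 × *c*) = 0/0, which is undefined for any *a* and *c*.

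**Step 2. The same as a regression.** A logistic model was fitted to 500 simulated victim-only records with a random binary factor (259 with, 241 without) and the outcome equal to 1 throughout. It gave an intercept of 27.2 (standard error about 51,000) and a slope of 9.5 (standard error about 4,170,000). These are numerical artefacts of a constant outcome. Extra records do not change this.

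**Step 3. What a population denominator would add.** From Table 1:

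- Residents: 314,103 + 116,992 + 139,978 + 70,542 = 641,615.
- Males, reading the sex ratio as females per 1,000 males: population × 1,000/(1,000 + sex ratio), summed over blocks, is 160,502 + 58,908 + 72,340 + 34,062, about 325,813 after rounding. Females: 641,615 − 325,813 = 315,802.

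The article does not give the bite incidence or the male share of cases, so both are assumed over a range. Two years at 100 per 100,000 per year give 2 × 641,615 × 100/100,000 ≈ 1,283 cases. If 60% are male, the rate ratio is (0.60/0.40) × (315,802/325,813) = 1.454. The grouped odds ratio, with two resident-years per person as denominator, is also 1.454.

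| Assumed male share | Rate ratio | Odds ratio, 100 per 100,000 per year | Odds ratio, 1,000 per 100,000 per year |
|---|---|---|---|
| 50% | 0.969 | 0.969 | 0.969 |
| 60% | 1.454 | 1.454 | 1.459 |
| 70% | 2.262 | 2.263 | 2.279 |

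Once a denominator is used, a ratio for sex exists, and the odds ratio is practically the rate ratio.

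**Step 4. Which factors have a margin.** Table 1 supports block, sex, Scheduled Tribes status and rural residence. Calendar month needs only person-time. Age would need census age tables by block, which Table 1 does not contain. Footwear, bed-net or torch use, which the Discussion names as preventive measures, have no population margin in the article. Venomous or non-venomous bite, site of bite and signs of envenomation belong to a bite and have no counterpart in an unbitten person.

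**The case against.** The strongest reply is that the article already uses a population denominator. The primary incidence outcome is expressed per 100,000, and the regression sentence does not say that the model is person-level and fitted to the forms alone. Cases set against census non-cases give valid grouped odds ratios, as Step 3 shows. This stands in part: a reader might infer that no incidence ratio of any kind could be obtained, and that would go too far. It does not remove the mismatch, because the article never connects the denominator to the regression, and the connection would serve only the few factors with census margins.

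A second reply is that a condensed article leaves detail to the full protocol or analysis plan. That would answer a complaint about missing detail. Here the article states the outcome, the effect measure and the data source, and those three do not fit together.

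Three further inferences are tempting and are not supported:

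- **That community prevention messages would depend on this regression.** Phase II bases the education material on gaps found in the focus groups and on the literature, and takes the preventive measures from the 2017 treatment guidelines.
- **That the primary comparison is undermined.** The before-and-after comparison of incidence and case fatality does not use this model.
- **That a bivariate model is itself an error.** Unadjusted associations are a legitimate descriptive step, and adjusted models may be specified in a document not shown.

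**Conclusion.** The point holds in limited form. On the data the article describes, an odds ratio for being bitten is not identifiable, whatever the number of cases. With a population denominator, which the plan does not link to this model, ratios become available for a few census factors. For exposures without a population margin, no assessment as a risk factor for being bitten is possible.

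Severity is moderate. The analysis is announced in the plan and cannot be run as written, but it is neither a primary nor a secondary outcome, and none of the four stated objectives is to identify risk factors.

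The conclusion rests on the article's account of its data sources being complete as regards unbitten people. If the full protocol contains a quantitative sample of unbitten residents, the sentence would need to name it. The figures in Step 3 depend on assumed incidence and male share and serve only to show that a grouped ratio exists; the conclusion does not depend on them.

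**What to change.** Replace the regression sentence with the following:

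- **Model.** Poisson or negative binomial regression of recorded bite counts by block, sex and calendar month, with log resident person-years as offset. Add age group if census age tables by block are obtained.
- **Denominator.** Census populations projected from 2011 to the study years, which begin in 2020, with the projection method stated.
- **Measure.** Rate ratios of recorded bites. The word *recorded* matters because the Discussion acknowledges that facility-based collection may under-report.
- **Odds ratios.** Keep them only for outcomes that vary among victims, such as envenomation, severe complication, referral or death, and label them as associations among victims.

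The cost is a change of analysis wording and the preparation of projected denominators; no new recruitment is needed. There are two drawbacks. Exposures without a population denominator can only be described, and the projected person-years are approximate. If the investigators want to study behavioural exposures as risk factors, they would need a comparison sample of unbitten residents, which is a change of design.
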